### Background/Rationale/Purpose

Depression is common among young, low-income mothers and has negative repercussions on children. Additionally, this population of mothers lacks access to quality mental health services – making a prevention intervention potentially important. We are conducting a multi-year RCT of a Head Start-based intervention model developed as part of [name] and [name] K23 awards. PSE represents an integrated identification and intervention system based on the construct of screening, brief intervention, and referral to treatment (SBIRT). Within the case management services of Head Start, eligible mothers will be randomized to receive either usual care or PSE. The basic steps of PSE are: screening to determine the severity of one's depressive symptoms; a problem-solving intervention

for those at risk for depression; and referral to more definitive services for those initially in the at risk group, who have worsening symptoms over time.

The specifics of PSE have been modified and field-tested over the previous four years (primarily in Head Start, under another BUMC IRB protocol H-25084). Activated referrals to further care incorporate principles of motivational enhancement that have been demonstrated to improve engagement with care in other settings and for other medical conditions. We will conduct an efficacy RCT, involving 230 Head Start mothers. Over a 12-month follow up period, we aim to:

1. Improve mothers' problem solving skills (primary outcome)
2. Decrease the incident rate of episodes in which mothers experience moderate to severe depressive symptoms and reduce depressive symptoms over time (primary outcome)
3. Increase mothers' likelihood of engaging with primary care or specialty mental health services if referred (secondary outcome)
4. Improve parental functioning, as assessed by children's missed Head Start school days (secondary outcome).

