#### Summary of inclusion criteria

1. Family enrolled in Head Start, and child expected to attend Head Start activities for at least 6 months of the 12- month follow-up period.
2. Family without imminent plans to relocate
3. Mother is comfortable in English or Spanish.
4. Parent/guardian who has a child that attends Head Start
5. Child attending Head Start and is between the ages 0-5
6. Screen positive to 2-question depression screener (PHQ2), or have a past history of depression
7. Screen Negative for current MDE using the M.I.N.I MDE Module.
8. Ability to provide informed consent.
9. Not suicidal

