  - d. For those individuals who refuse screening, are not eligible or opt not to participate, we will record only their temporary study code on the recruitment screen. We will submit this list of temporary study codes to Head Start personnel for two reasons: 1) to avoid inadvertent re-approaching; and 2) so that Head Start can supply the study team with an anonymized demographic description of this population with a de-identified list of demographic characteristics, (Attached in the study binder). Specific variables will include only those that Head Start keeps for programmatic reasons (the equivalent of existing clinical data): age, language spoken, place of birth, race, ethnicity, education, work status, marital status, household type (single or double-headed household), number of people in household, living situation, income, health insurance status, type of government assistance.
4. Written Informed Consent: After the two screens are administered and the potential subject is found to be eligible, the subject will be enrolled (if willing) into either the RCT or into a small supplemental pilot study of 'PSE Lite.' Immediately following the signing of the consent form, the following will happen:
- a. Subjects will be administered either the MacCAT-CR immediately after the consent form in order to ensure that subjects with limited cognitive capacities and/or major mental illness, including psychosis, are safeguarded from being in the study.
  - b. Subjects will be screened for suicidal ideation in order to safeguard subjects with high suicidal ideation. Our crisis protocols will be activated as necessary (Crisis Management Plan, Domestic Violence Protocol, Referral of Clients with Trauma or Substance Use – each protocol is provided in the study binder).
5. Once participants have completed the safeguards outlined in above, we will collect the following data from all mothers enrolled in the study *prior to* randomization. The interviews will be completed in private rooms at the Head Start center, or in subjects' homes (subjects' choice). The Baseline Survey will comprise the following valid and reliable scales:
- a. Children with Special Health Care Needs Screener

- b. Perceived Stress Scale
  - c. M.I.N.I. Depression Module (current or recurrent Major Depressive Episode (We will use the data from the second verbal screen for this. We have added this permission to the written consent form.))

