8. Outcome assessments: Each subject will have a 12-month follow up period, during which blinded research assistants will assess outcome measures. Follow-up data collection will begin 2 months after baseline because a full, 6-session course of PSE typically lasts 6-8 weeks. To limit attrition, we will employ a combination of monetary incentives and postcard reminders. Through these strategies, approved by the BUMC IRB in our pilot work, we have been able to maintain follow up rates > 85% across all relevant ongoing studies (there is a separate section on participant compensation in the protocol manual).

Baseline, 6-month, and 12-month assessments will take place in person with a staff RA. We will administer the QIDS and mental health service use questions on a bimonthly basis throughout the study period, and this will be done by telephone by a staff RA.

The 6-month interview will comprise the following valid and reliable scales:

- a. Perceived Stress Scale
- b. M.I.N.I. Depression Module
- c. QIDS
- d. Mental Health Service Use questions (adapted from Collaborative Psychiatric Epidemiology Surveys)
- e. Social functioning (Social Adjustment Scale-Self Report)
- f. Parenting Stress Index
- g. Problem Solving Questions (Social Problem Solving Inventory)
- h. Coping Questions (Brief COPE)
- i. Pearlin Mastery Scale
- j. Behavioral Activation for Depression Scale
- k. Rosenberg Self-Esteem Scale

The 12-month interview will comprise the following valid and reliable scales:

- a. Perceived Stress Scale
- b. M.I.N.I. Depression Module
- c. QIDS
- d. Mental Health Service Use questions (adapted from Collaborative Psychiatric Epidemiology Surveys)
- e. Social functioning (Social Adjustment Scale-Self Report)
- f. Problem Solving Questions (Social Problem Solving Inventory)
- g. Coping Questions (Brief COPE)
- h. Pearlin Mastery Scale
- i. Behavioral Activation for Depression Scale
- j. Rosenberg Self-Esteem Scale
- k. Recent Life Changes Questionnaire

- I. Mood, anxiety and alcohol and other substance use, modules of the SCID

RA's will be trained not to leave telephone messages, and to introduce themselves as from "BMC" so as to ensure confidentiality.

9. At 6-months post randomization, parents and Head Start teachers will be asked to fill out the Social Skills Rating System (SSRS) with reference to all 3-5 year-old Head Start children of enrolled parents.
10. We will assess rate of absenteeism from Head Start for children of mothers who are in our study.

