#### Outcome measures (\*denotes primary outcome measure)

| Outcomes                                                      | Operationalization of variable                                    | Timing of data collection after baseline |
|---------------------------------------------------------------|-------------------------------------------------------------------|------------------------------------------|
| i. Problem Solving Skills*                                    | Calculated problem solving index from SPSI-R                      | 6, 12 months                             |
| ii. Incident rate of moderate to severe symptomatic episodes* | QIDS score $\geq 11$ , corresponding to 'moderate' symptomatology | 2, 4, 6, 8, 10, 12 months                |
| iii. Depressive symptoms over time*                           | Mean QIDS scores over time                                        | 2, 4, 6, 8, 10, 12 months                |
| iv. Social and parenting functioning                          | Mean SAS-SR and PSI scores                                        | 6, 12 months                             |
| v. Receipt of mental health services                          | Standardized questionnaire                                        | monthly recall                           |
| vi. Head Start attendance                                     | Head Start records, analyzed as monthly absence rates             | monthly reports                          |

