### Sample Size Justification

Based on empiric longitudinal data that we have collected among a cohort of Head Start mothers, we describe the size of detectable interventional effects with adequate statistical power for each primary outcome. All estimates assume 80% power and a two-sided alpha of 0.05.

- i. Problem solving skills. The mean problem solving (SPSI-R) score among mothers in our observational study is 12.2, (SD 2.5); women with  $\geq$  moderate depression symptoms have a mean score of 14.7 (SD 2.2) and those with  $\leq$  mild symptoms have a mean score of 9.8 (SD 2.8;  $p > 0.0001$ ). Using a two-sample t-test, a sample size of 100 per group will be able to detect a very granular one-point difference in mean SPSI-R scores between study groups (a standardized effect size of 0.4).

- ii. Incident rate of moderate to severe symptomatic episodes. Using poisson regression analysis, with 100 subjects in each study group and a poisson rate of 1.2 spikes per 5 follow-up assessments in the control group (according to our current data), we can detect a reduction in the rate of spikes to 0.8 in the treatment group – a 33% reduction in symptomatic episodes.
- iii. Depressive symptoms over time. In our longitudinal data, we have observed the following mean QIDS scores for each follow-up month and assume these values for the control group in the planned study: 8.2; 7.6; 7.5; 6.9; 7.2 (common SD, 5.9). We hypothesize that the following mean QIDS scores in the treatment group would be achievable and clinically significant: 7.2; 6.6; 5.5; 4.4; 4.2, resulting in a mean difference of 3 points in QIDS scores across study groups (note: a 3-point difference in QIDS scores, in the majority of cases, would move a subject across a clinical cutoff corresponding to mild, moderate or severe symptoms). Using a two group repeated measures design analyzed by generalized estimating equations or mixed linear models, noting within-subject correlations of 0.7 for values separated in time by one month and 0.6 for those separated for two months or more in our longitudinal analysis), we can detect the above differences in the means between groups over time with 100 subjects per study group.

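### No pre-randomization absence measure is named for Head Start attendance (Aim 4), although the same records could supply one for some children: a cheap gain in precision is missed

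*Protocol*

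**What the plan says.** Aim 4 in the Background section treats children's missed school days as the measure of parental functioning, as a secondary outcome. The outcome measures table (row vi) operationalizes it as "Head Start records, analyzed as monthly absence rates". The timing entry is monthly reports, in a column headed "Timing of data collection after baseline". The Procedure section (item 10) adds only: "We will assess rate of absenteeism from Head Start for children of mothers who are in our study". It gives no time window.

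What is gathered before randomization is listed in the Procedure section under "The Baseline Survey will comprise the following valid and reliable scales". That list includes problem solving (SPSI), depressive symptoms (QIDS), social adjustment (SAS-SR) and mental health service use. It does not include attendance.

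Two inclusion criteria bear on whether earlier records exist. Item 5 reads "Child attending Head Start and is between the ages 0-5". Item 1 looks forward: "child expected to attend Head Start activities for at least 6 months of the 12- month follow-up period". Neither sets a minimum period of attendance before entry.

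The Data Analysis section gives models for the three primary outcomes. For secondary outcomes it promises an intention-to-treat comparison of the groups, with no model or covariates for attendance.

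**The concern.** Absence is likely to differ between children for lasting reasons that have nothing to do with the intervention, such as chronic illness or transport. A child's own earlier absence rate is the natural covariate for removing that variation. For a child already enrolled, it sits in the same administrative record that will supply the outcome. Most other repeated outcomes in the table have a baseline measurement named in the protocol, and attendance has none.

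At stake is the precision of the measure named for Aim 4, which is also one of the few outcomes that mothers do not report themselves. Randomization is stratified by site and depression history but not by earlier absence, so the arms can differ by chance on it. The sample size was justified for the primary outcomes only, so attendance has no stated power.

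**Working it through.** **Is there a baseline counterpart for each outcome in the table?**

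| Outcome | Baseline measure named in the Procedure section |
|---|---|
| Problem solving (SPSI-R) | Yes |
| Symptomatic episodes and mean score (QIDS) | Yes |
| Social and parenting functioning | SAS-SR yes; PSI no |
| Mental health services | Yes |
| Head Start attendance | No |

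**The plan's own figure, as a frame.** No sample size, SD or correlation is given for attendance. The nearest stated calculation is for SPSI-R: a 1-point difference, SD 2.5, 100 per group. On the assumptions, the plan says "All estimates assume 80% power and a two-sided alpha of 0.05".

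- n per group = 2 × (1.960 + 0.842)² / 0.4² = 98.1, so 99. The t-test version gives 99.1, so 100. The stated figure reproduces, with power at 100 per group of 0.80 to 0.81.
- Detectable difference at 100 per group without a covariate: (1.960 + 0.842) × √(2/100) = 0.396 SD.

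**Adjusting for earlier absence.** With r the correlation between a child's earlier and later absence rates, the residual variance factor is 1 − r², the equivalent sample multiplier is 1/(1 − r²), and the detectable difference is 0.396 × √(1 − r²). The values of r are assumed.

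| r | 1 − r² | Variance removed | Sample multiplier | Detectable difference |
|---|---|---|---|---|
| 0.3 | 0.91 | 9% | 1.10 | 0.378 SD |
| 0.5 | 0.75 | 25% | 1.33 | 0.343 SD |
| 0.7 | 0.51 | 49% | 1.96 | 0.283 SD |

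**If only half the children have an earlier record** (also assumed), the average residual variance is 0.5 × (1 − r²) + 0.5:

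| r | Average factor | Variance removed | Sample multiplier |
|---|---|---|---|
| 0.3 | 0.955 | 4.5% | 1.05 |
| 0.5 | 0.875 | 12.5% | 1.14 |
| 0.7 | 0.755 | 24.5% | 1.32 |

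These figures assume one common residual variance. Weighting children with and without records by their own precision gives factors 1 / [0.5/(1 − r²) + 0.5] = 0.953, 0.857 and 0.675, so somewhat more is gained at the higher correlations.

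**Is the range of r reasonable for monthly data?** Suppose any two months of one child's absence correlate at ρ. The mean of p earlier months and the mean of m later months then correlate at ρ / √{[(1 + (p − 1)ρ)/p] × [(1 + (m − 1)ρ)/m]}.

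- ρ = 0.2, p = 1, m = 6: 0.2 / √(1 × 0.333) = 0.35.
- ρ = 0.3, p = 3, m = 12: 0.3 / √(0.533 × 0.358) = 0.69.

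Modest monthly correlations therefore span about the assumed range. The result depends on how many earlier months exist.

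**The case against.** The strongest reply is that the protocol excludes nothing. The column header covers all six rows, including SPSI-R and QIDS, which are measured at baseline, so it lists follow-up times and does not say that no earlier value exists. The baseline list is an interview survey, and a records-based item would not necessarily appear there. The choice of covariates for a secondary outcome commonly sits in the statistical analysis plan, which is not at hand. Most of this stands. A reader might infer that the trial will compare raw follow-up absence, or that earlier records are deliberately set aside. The documents support neither, because they give no attendance model at all.

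What does not fall away is the data window. An analysis plan can name a covariate, but it cannot by itself extend a records request or the scope of consent. Those belong in the protocol, and the protocol names no window before randomization.

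A second reply is that other information already helps: the baseline survey has a screener for special health care needs and demographics, and randomization is within site. This also stands. It rules out saying that a chance imbalance could not be corrected, though these are only indirect substitutes for the child's own absence rate.

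A third reply is that the size of the gain is assumed throughout, and that a child attending at entry may have only just enrolled. Both points are right, which is why the range runs down to r = 0.3 and to half the children having records.

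**Conclusion.** The point holds as a modest, optional improvement. The protocol names no pre-randomization attendance measure, and some children's records could supply one.

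The likely benefit runs from negligible (4.5% of the variance, at r = 0.3 with records for half the children) to substantial (49%, at r = 0.7 with records for all). It rests on an assumed correlation, an assumed share of children with records, and a simple adjustment for one covariate. The documents fix none of these. The 100 per group is borrowed from the primary outcomes as a frame.

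It would be wrong to read this as a threat to validity. Under randomization an unadjusted comparison of absence is unbiased, and nothing in the protocol contradicts itself here. What is lost is efficiency in a secondary outcome for which no power was claimed.

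**What to change.** In row vi of the outcome table and item 10 of the Procedure section, state that the attendance records requested will cover any months before randomization in the current program year as well as follow-up. Check that the consent wording covers those earlier months, and amend it if not.

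Then state that the comparison of post-randomization absence will adjust for the child's earlier absence rate, with an indicator for children who have no earlier record, and for the stratification factors (site and depression history). This should be fixed in advance and not made conditional on an observed baseline difference.

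The cost is a wider date range in a records request that is already planned, plus the consent wording. Newly enrolled children will contribute little or nothing to the gain.

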### Sample Size Justification

Based on empiric longitudinal data that we have collected among a cohort of Head Start mothers, we describe the size of detectable interventional effects with adequate statistical power for each primary outcome. All estimates assume 80% power and a two-sided alpha of 0.05.

- i. Problem solving skills. The mean problem solving (SPSI-R) score among mothers in our observational study is 12.2, (SD 2.5); women with  $\geq$  moderate depression symptoms have a mean score of 14.7 (SD 2.2) and those with  $\leq$  mild symptoms have a mean score of 9.8 (SD 2.8;  $p > 0.0001$ ). Using a two-sample t-test, a sample size of 100 per group will be able to detect a very granular one-point difference in mean SPSI-R scores between study groups (a standardized effect size of 0.4).

- ii. Incident rate of moderate to severe symptomatic episodes. Using poisson regression analysis, with 100 subjects in each study group and a poisson rate of 1.2 spikes per 5 follow-up assessments in the control group (according to our current data), we can detect a reduction in the rate of spikes to 0.8 in the treatment group – a 33% reduction in symptomatic episodes.
- iii. Depressive symptoms over time. In our longitudinal data, we have observed the following mean QIDS scores for each follow-up month and assume these values for the control group in the planned study: 8.2; 7.6; 7.5; 6.9; 7.2 (common SD, 5.9). We hypothesize that the following mean QIDS scores in the treatment group would be achievable and clinically significant: 7.2; 6.6; 5.5; 4.4; 4.2, resulting in a mean difference of 3 points in QIDS scores across study groups (note: a 3-point difference in QIDS scores, in the majority of cases, would move a subject across a clinical cutoff corresponding to mild, moderate or severe symptoms). Using a two group repeated measures design analyzed by generalized estimating equations or mixed linear models, noting within-subject correlations of 0.7 for values separated in time by one month and 0.6 for those separated for two months or more in our longitudinal analysis), we can detect the above differences in the means between groups over time with 100 subjects per study group.

Therefore, with an analyzable sample of 100 subjects per study group, we will be able to detect with adequate statistical power differences in problem solving scores, incident rates of elevated QIDS scores, and mean QIDS scores over time that are of clear clinical relevance. Based on our current data, we estimate that 20% of mothers approached will refuse participation; 70% will meet eligibility criteria; and we will experience a 15% attrition rate over the course of the study. Therefore, to ensure that we assess outcomes in 200 study subjects, we will approach 410 subjects and randomize 230. This sample size will be readily available from our ABCD Head Start sites, which average 100 families per site.

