### Design

At present, all Head Start mothers are given social work and case management services and education by the Head Start team regarding the importance of physical and mental health care. Mothers are screened for mental health needs during their "strength and needs assessment" by the case management staff and given referrals to care when necessary. However, there is no systematic depression prevention strategy, and there is no tested, evidence-supported mechanism to get depressed parents quality mental health care.

Study design. Parallel group, RCT involving mothers whose children attend Head Start - a comprehensive preschool program for low-income children birth to 5. Eligible mothers will be randomized to receive PSE or standard of care at Head Start. Both groups will be followed for 12 months.

Participants. 230 Head Start mothers (115, PSE; 115, control) will be enrolled in the at-risk stratum.

Randomization. The unit of randomization will be the mother. Investigators and data collectors will be blinded to study allocation. We could have chosen a number of study designs, including cluster randomization by caseworker or Head Start center. Cluster randomization, however, has its own set of methodologic shortcomings, notably post-randomization selection bias. Because we also expect high intra-class correlation among families within the same Head Start center, a cluster design on this basis would create unrealistic sample size requirements. Conversely, the only substantial drawback of a parallel design would be a conservative bias in favor of the control arm due to intervention spillover. However, because control subjects will not have access to trained educators, we anticipate such effects to be minimal. Randomization will occur independently within each Head Start site, within strata defined by the presence or absence of depression history. We will randomize 1:1 within randomly varying blocks of 2 and 4.

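### The SPSI-R standard deviation of 2.5 contradicts the subgroup figures beside it, which imply about 3.5; power for a one-point difference is then about 52%, not 80%

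*Protocol*

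**What the plan says.** Protocol, Sample Size Justification, opens by stating that "All estimates assume 80% power and a two-sided alpha of 0.05". Item i then reports, from the team's observational cohort of Head Start mothers, that "The mean problem solving (SPSI-R) score among mothers in our observational study is 12.2, (SD 2.5"). The same sentence splits the cohort by depressive symptoms: women at or above "moderate depression symptoms have a mean score of 14.7 (SD 2.2") and those at or below "mild symptoms have a mean score of 9.8 (SD 2.8").

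The power statement follows: "Using a two-sample t-test, a sample size of 100 per group will be able to detect" a one-point difference in mean SPSI-R score, described as "a standardized effect size of 0.4". Allocation is equal (Design: "We will randomize 1:1 within randomly varying blocks of 2 and 4").

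The Data Analysis section plans the same unadjusted two-sample t-test for this outcome. Linear regression is used only if the groups differ significantly at baseline. The Outcomes table stars problem-solving skills as a primary outcome and lists it first.

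**The concern.** An effect size of 0.4 for one point is 1/2.5, so the whole power claim for this outcome rests on the SD of 2.5. That SD is presented as the spread among all mothers in the cohort. Yet the two symptom subgroups have SDs of 2.2 and 2.8 and means 4.9 points apart. When two groups of similar size and that separation are combined, the overall SD must be clearly larger than either group's own SD. A value of 2.5, midway between 2.2 and 2.8, looks like an average of the within-group SDs.

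If the SD is too small, the trial has roughly even odds of missing a true one-point effect on a primary outcome. Problem solving is also a hypothesized mediator in the January 2018 appendix, so a null result could be misread as evidence that the intervention does not act on its supposed mechanism.

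**Working it through.** **Inputs** (all from Sample Size Justification, item i, unless noted): overall mean 12.2, SD 2.5; moderate or worse 14.7, SD 2.2; mild or less 9.8, SD 2.8; difference 1 point; 100 per group; two-sided alpha 0.05 and 80% power (opening of that section); 1:1 allocation (Design).

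**1. Reproduce the protocol's figure.** Effect size = 1/2.5 = 0.4. The normal-approximation sample size is 99 per group. Power at 100 per group is 80.7% by the normal approximation and 80.4% by the noncentral t. The stated claim therefore follows from SD 2.5.

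**2. Share in the higher-symptom group.** The two categories are exhaustive, so the overall mean fixes the share p:

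p = (12.2 − 9.8)/(14.7 − 9.8) = 2.4/4.9 = 0.490.

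**3. Overall variance** (law of total variance):

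- Within groups: 0.490 × 2.2² + 0.510 × 2.8² = 6.37, an SD of 2.52.
- Between groups: 0.490 × 0.510 × 4.9² = 6.00, an SD of 2.45.
- Total: 12.37, so the overall SD is 3.52.

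The within-group SD of 2.52 matches the printed 2.5. The between-group part alone contributes 2.45, so a true overall SD of 2.5 would leave almost no variation inside the subgroups.

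**4. Rounding.** Moving all five other inputs to the ends of their rounding intervals (±0.05) keeps the overall SD between 3.44 and 3.59, and power between 50% and 54%. Rounding cannot produce 2.5.

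**5. Consequence at SD 3.52.**

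- Effect size for one point: 1/3.52 = 0.28.
- Power at 100 per group: 51.6% (noncentral t); 52.0% (normal approximation).
- Difference detectable with 80% power at 100 per group: 1.40 points.
- Needed per group for one point at 80% power: 195 (normal approximation).
- Power if all 115 randomized per group were analyzed: about 58% (normal approximation).

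**6. Sensitivity to the trial's symptom mix.** The share p in the trial is an assumption. The subgroup means and SDs are held at the protocol's values, with 100 per group, one point and the noncentral t.

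| Share moderate or worse | Overall SD | Power | Detectable difference at 80% |
|---|---|---|---|
| 0% | 2.80 | 71% | 1.11 |
| 10% | 3.11 | 62% | 1.24 |
| 24% | 3.39 | 55% | 1.35 |
| 44% (largest SD) | 3.53 | 51% | 1.40 |
| 49% | 3.52 | 52% | 1.40 |
| 90% | 2.70 | 74% | 1.08 |
| 94% | 2.52 | 80% | 1.01 |

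The 24% row reads the protocol's 1.2 elevated scores per 5 assessments (item ii: 1.2/5 = 0.24) as a prevalence, which is itself an assumption. The overall SD falls to 2.5 only when the share reaches about 94% to 95%.

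**The case against.** The strongest reply is that 52% is close to the worst case and depends on a 49% share that may not be real. The overall mean of 12.2 is nearly the plain average of the two subgroup means, (14.7 + 9.8)/2 = 12.25. If 2.5 is a plain average of the SDs, 12.2 may be a plain average of the means and say nothing about the mix. The protocol's other cohort figures point to a lower share: at 24% the overall mean would be 9.8 + 0.24 × 4.9 = 11.0. The trial also excludes mothers in a current major depressive episode, so its mix may differ from the cohort's. All of this stands. It means the overall mean deserves checking too, and that power is better given as a range. It does not rescue the claim: no share below about 94% gives 80% power, and such a share would be hard to square with the control-group QIDS means of 6.9 to 8.2 assumed in item iii, when moderate symptoms start at 11.

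A second reply is that 100 per group still gives 80% power for 0.4 SD, and that only the conversion into points is wrong. That is correct. A detectable difference of 1.4 points is also under a third of the 4.9-point gap between the subgroups, so it may still be worthwhile. But the protocol makes its claim in points and presents it as "detect a very granular one-point difference in mean SPSI-R scores between study groups"; that statement is wrong as written.

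A third reply is that 2.5 could serve as a residual SD in an adjusted analysis. If baseline SPSI-R correlated 0.7 with follow-up (assumed), power for one point would return to about 80%; at 0.5 it would be about 64%. However, the protocol labels 2.5 as the SD among all mothers and plans an unadjusted t-test, with adjustment only after a significant baseline difference.

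**Conclusion.** The concern holds. The overall SD of 2.5 cannot be true alongside the overall mean and subgroup figures in the same sentence; those figures imply 3.52 (3.44 to 3.59 allowing for rounding). On that SD, 100 per group give about 52% power for one point under the planned unadjusted t-test, and the difference detectable with 80% power is about 1.4 points.

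The 52% assumes that the trial shares the cohort's implied mix of 49% at moderate or worse, and that the subgroup means and SDs carry over to the trial. If the share is anywhere from none to about half, power is 51% to 71% and the detectable difference about 1.1 to 1.4 points. The statement that 100 per group detect 0.4 SD remains correct; the statement that this equals one point does not.

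**What to change.** Recompute the overall SPSI-R mean and SD from the observational dataset, which the investigators hold, preferably restricted to mothers who would meet the trial's eligibility criteria. Then restate item i in one of two ways: keep 100 per group and 0.4 SD and give the matching difference in points (about 1.4 if the SD is confirmed near 3.5), or keep one point and state the power actually available (about 52% at that SD). If the trial's symptom mix is uncertain, give the range. Carry the correction into the closing paragraph of the Sample Size Justification, which concludes that power is adequate for this outcome.

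If the sponsor wants to recover precision, it can prespecify an analysis adjusted for baseline SPSI-R, which is already collected, and base the power statement on that analysis with the baseline to follow-up correlation taken from the cohort.

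The cost is a short recalculation and a text change. Restating the detectable difference or the power requires no extra enrolment; keeping both one point and 80% power with the unadjusted test would require about 195 analyzable mothers per group.
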